# The treatment regimens in each study group will be as follows:

1. Ethambutol (800 mg) and Isoniazid (300 mg) daily for six months, self-administered, collected once in fifteen days.
2. Isoniazid (300 mg) daily for 3 years (in lieu of lifelong prophylaxis) with fortnightly collection of drugs

Subjects in both study groups will receive 10 mg of Pyridoxine daily during treatment.

**Follow-up**

During chemoprophylaxis

All enrolled patients will be followed up regularly to monitor general clinical status, adverse effects, adherence to drugs and development of active tuberculosis. Patients will be called to the clinic three monthly for a thorough clinical assessment and measurement of weight (see table). During each clinic visit, patients will be verbally screened for chest symptoms. In the presence of chest symptoms, the patient will be thoroughly evaluated clinically, and investigated for tuberculosis by radiological examination and 3 sputum specimens for smear and culture.

During each follow up visit the patient will asked for any symptoms or signs of drug toxicity. Details of any adverse reactions and their management will be recorded on a standardized toxicity form. Adverse reactions will be appropriately managed.

Adherence to the assigned regimen will be checked by detailed questioning of patients, return of empty drug packs, and by examination of spot urine samples for acetyl isoniazid. Non-adherent patients will be counseled regarding importance of treatment regularity and monitored closely. If a patient fails to attend the on the due date for drug collection, a letter will be posted, following which a health visitor or social worker will visit his/her home in case there is no response within a week.

Post Chemoprophylaxis

Patients will be followed up for a period of three years from the time of admission to the study. Clinical examination and relevant investigations will be done 3 monthly. Patients suspected to have tuberculosis at any time will be fully investigated and treated appropriately. Any positive culture will be subjected to drug susceptibility tests. If a patient dies, a verbal autopsy will be conducted to ascertain the cause of death**.**

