**Study Design**

The study will be a two-armed prospective randomized clinical trial among HIV- positive patients without active tuberculosis. Enrolled patients will be assigned to one of the two unsupervised self-administered treatment regimens i.e. EH for 6 months or INH alone for 3 years. At the end of a 3-year follow-up, incidence of TB and overall mortality will be compared in each group.

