## Investigation and follow up

| Clinical Evaluation | Sputum smear and culture | Mantoux Test | Urine for Alb, Sugar, Ac-INH | Hemogram, Renal & Liver function test | Chest  X-ray | CD4/CD8 Viral load, Immunol. Investigns. |
| --- | --- | --- | --- | --- | --- | --- |
| 0 month & every 3rd month till completion of study, and whenever patient is symptomatic | 0 month (3 specimens), 6,12,18,24, 30,36 mths (2 spec) and if ordered by doctor | 0 month and at clinical diagnosis of TB | 0 month, every month till 36 months | 0 month & if any toxicity | 0 month, 6,  12, 18, 24, 30, 36 months and if ordered by doctor when patient is symptomatic | 0 month, 6, 12, 18, 24, 30 and 36 months |

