### Radiographic and/or Clinical Deterioration:

a) If a patient has been admitted to the preventive therapy study and baseline sputum culture/s are reported as positive, the patient should be called up to the clinic, re-evaluated and started on chemotherapy (Category I or II depending on duration of treatment). If the patient is not suitable for Study XX, then he/she can be treated in Zero study – adequate treatment for these patients must be ensured.

b) If during the treatment period, the patient becomes symptomatic, clinical examination will be done, an X-ray ordered and 3 sputa collected for smear and culture. A course of antibiotics will be prescribed and a repeat chest X-ray done after 15 days. If the symptoms are not respiratory in origin, then evaluation and referral to the appropriate department for further investigations will be done. All attempts will be made to make a definite diagnosis including investigations like pleural tap, lymph node biopsy, ultrasound abdomen and CSF examination where necessary. The treating doctor, in consultation with TRC clinic physicians, will decide about the need for anti-tuberculosis treatment. The case will be put up to the Weekly Panel for a decision. Normally, patients diagnosed to have tuberculosis will be admitted to the Chemotherapy study (if eligible and suitable) and treated with Category II. Modifications may be made after the culture and sensitivity results are available.

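### Defaulter tracing is tied to drug collection, so after month 6 it runs only in the isoniazid arm, and capture of TB and deaths can differ by arm

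*Protocol*

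**What the plan says.** - **Regimens.** Protocol, Study Design: "unsupervised self-administered treatment regimens i.e. EH for 6 months or INH alone for 3 years". No placebo is described.
- **Drug collection.** The regimen list gives "Ethambutol (800 mg) and Isoniazid (300 mg) daily for six months, self-administered, collected once in fifteen days" for the EH arm and "Isoniazid (300 mg) daily for 3 years (in lieu of lifelong prophylaxis) with fortnightly collection of drugs" for the other.
- **Tracing.** Follow-up, During chemoprophylaxis: "If a patient fails to attend the on the due date for drug collection, a letter will be posted". A home visit follows if there is no response within a week. This is the only tracing rule in the document.
- **After treatment.** Follow-up, Post Chemoprophylaxis: "Patients will be followed up for a period of three years from the time of admission to the study" and "Clinical examination and relevant investigations will be done 3 monthly". No tracing rule is given here. The same paragraph says that TB suspected at any time will be investigated, and that a death leads to a verbal autopsy.
- **Common schedule.** The Investigation and follow up table does not distinguish the arms. It has clinical evaluation every third month and when symptomatic, sputum and chest X-ray six-monthly, and urine "0 month, every month till 36 months".
- **Deciding on TB.** Radiographic and/or Clinical Deterioration, item b), sets out the work-up for a patient who becomes symptomatic while on treatment. The treating doctor consults clinic physicians, and then "The case will be put up to the Weekly Panel for a decision". The protocol does not say what the panel knows about the regimen.
- **Endpoints.** TB is primary; adverse reactions and mortality are secondary. Analysis is by intention-to-treat, with person-year rates and the log-rank test. The sample size allows one drop-out rate, 10% per year, without splitting it by arm.

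**The concern.** The rule that keeps patients in the study is attached to treatment, not to follow-up. Treatment length is what differs between the arms, so for 30 of the 36 months the protocol prescribes active retention in one arm and none in the other. Scheduled tests find TB only in patients who attend, and a verbal autopsy needs the death to be known. If patients who stop attending are more likely to be ill or dead, the EH arm would lose events that the isoniazid arm keeps. That would make EH look better than it is, hiding a real benefit of long isoniazid or suggesting an EH advantage that does not exist. Intention-to-treat keeps patients in their assigned group; it does not supply outcomes for patients who were never found.

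Two features add to this. Read literally, the symptomatic work-up and panel route also runs for 6 months in one arm and 36 in the other. And with such different regimen lengths and no placebo described, the doctor who brings a case to the panel would know the arm, while smear-negative TB calls for judgement.

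**Working it through.** The protocol gives no figure of its own on this point to reproduce. The check compares the rules by arm, counts contacts, and then asks what a bias would require.

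**1. Rules in force from month 6 to month 36**

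| Element | EH arm | Isoniazid arm |
| --- | --- | --- |
| Drug collection | ended at month 6 | fortnightly to month 36 |
| Letter and home visit after a missed collection | never triggered | triggered at any missed collection |
| Letter and home visit after a missed assessment | no rule | no rule |
| Item b) work-up and panel, as worded | treatment has ended | applies to month 36 |
| Suspected TB investigated at any time | yes | yes |
| Three-monthly evaluation, six-monthly sputum and X-ray, monthly urine | yes | yes |

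**2. Counts over these 30 months**

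- 30 × 30.44 = 913 days. Collections in the isoniazid arm: 913/15 = 61, 913/14 = 65, or 30 × 2 = 60 at two per month. EH arm: 0.
- Three-monthly evaluations at months 9, 12, …, 36: 10 in each arm.
- Sputum and X-ray rounds at months 12, 18, 24, 30, 36: 5 in each arm.
- Monthly urine tests: 30 in each arm, if done as tabled.

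The difference is therefore about 60 to 65 tracing triggers against none. The scheduled outcome tests do not differ.

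**3. What a bias would require**

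The following uses assumptions that are not in the protocol: equal true TB rates in both arms, and exponential drop-out in each arm at the protocol's 10% per year with 325 patients per arm.

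- Hazard of drop-out: h = −ln(0.9) = 0.1054.
- Person-years per arm over 3 years: 325 × (1 − 0.9³)/h = 835.9.
- Of these, months 0–6: 325 × (1 − 0.9^0.5)/h = 158.3. Months 6–36: 835.9 − 158.3 = 677.6.

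Suppose a further fraction f of EH cases and a further fraction g of EH person-time are lost after month 6. The apparent EH/isoniazid rate ratio is

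[158.3 + (1 − f) × 677.6] / [158.3 + (1 − g) × 677.6].

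- f = 0.20, g = 0.20 (loss unrelated to TB): 700.4/700.4 = 1.00, no bias.
- f = 0.20, g = 0.10: 700.4/768.1 = 0.91.
- f = 0.20, g = 0 (cases missed, all person-time kept): 700.4/835.9 = 0.84.
- With g = 0, f = 0.10 gives 0.92 and f = 0.30 gives 0.76.

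The g = 0 results are the extreme for a given f, provided some person-time goes with the lost cases. In that extreme, with a two-sided 5% test (also an assumption; the protocol states no level) and standard error √(1/e₁ + 1/e₂) for event counts e₁ and e₂, the false-positive rates for f = 0.10, 0.20 and 0.30 are about 6%, 9% and 15% at 3 per 100 person-years, and 7%, 15% and 29% at 7 per 100. These figures show how the problem would behave. They do not estimate its size.

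**The case against.** The strongest reply is that outcome assessment is largely common to both arms. The schedule table gives both arms the same evaluations, sputum cultures, X-rays and urine tests to month 36; suspected TB is investigated whenever it arises; and deaths get a verbal autopsy. Losses that are unrelated to TB take their person-time with them and leave the rate ratio unchanged. All of this stands, and it confines the point to tracing of non-attenders and TB found between scheduled visits. It does not remove the point: these provisions reach only patients who attend or whose death is known, and a missed EH assessment starts nothing.

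A reader might infer more than the protocol supports:

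- **That TB ascertainment as a whole differs by arm.** The common schedule contradicts this.
- **That the comparison is about 61 contacts against 10.** The isoniazid arm has the same 10 evaluations, and monthly urine would bring EH patients in monthly. The collections matter as tracing triggers.
- **That isoniazid patients are asked about symptoms and toxicity more often.** Screening is tied to clinic and follow-up visits, and nothing says that a drug collection is one. The fortnightly, monthly and three-monthly intervals serve different purposes and can coexist; what is missing is a statement of which are outcome assessments.
- **That the panel is unmasked.** The protocol is silent. It can be said only that no masking is provided for.
- **That the bias rivals the planned effect.** The Sample Size rates give 3/7 = 0.43, or 0.85 on the log scale. Even the extreme case with f = 0.20 gives ln(1/0.84), about 0.18, roughly a fifth of that.

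**Conclusion.** The point holds in a limited form and should be corrected. Following the tracing rule as written makes retention effort depend on arm for 30 of 36 months: about 60 to 65 tracing triggers in the isoniazid arm and none in the EH arm. The item b) work-up wording has the same 6-versus-36-month asymmetry and sits uneasily with the statement that suspected TB is investigated at any time. Loss to follow-up, and so capture of TB and deaths, can differ by arm in a trial whose drop-out allowance makes no distinction between arms.

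Whether this biases the comparison depends on the untraced loss being informative, which is plausible but not shown. The likely direction, on that assumption, is more TB found and fewer losses in the isoniazid arm. The size cannot be derived from the protocol. The lack of a masking provision is a secondary matter with no predictable direction. The tracing rule is fixed in the protocol, and no later analysis can recover patients who were not traced.

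**What to change.** 1. **Tracing.** In both arms to month 36, let a missed scheduled assessment trigger the same letter and home visit, in addition to the existing trigger of a missed drug collection.
2. **One ascertainment route.** Reconcile the Post Chemoprophylaxis paragraph with item b) of Radiographic and/or Clinical Deterioration, so that the TB work-up and panel route cover the whole follow-up in both arms. State, across Randomization and Dosing, the regimen list, Follow-up and the schedule table, which visits are outcome assessments common to both arms. Keep recording all adverse events whenever they are reported; limiting this to common visits would weaken safety data.
3. **Endpoint classification.** For the primary endpoint, have the existing Weekly Panel classify TB from a file without the regimen, the drug-collection record and the acetyl-isoniazid results. Because the panel also rules on treatment, keep this classification separate so that treatment decisions are unaffected.

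The cost is some extra letters and home visits by existing staff, clerical preparation of panel files, and a separate classification step for each suspected case.

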## Investigation and follow up

| Clinical Evaluation | Sputum smear and culture | Mantoux Test | Urine for Alb, Sugar, Ac-INH | Hemogram, Renal & Liver function test | Chest  X-ray | CD4/CD8 Viral load, Immunol. Investigns. |
| --- | --- | --- | --- | --- | --- | --- |
| 0 month & every 3rd month till completion of study, and whenever patient is symptomatic | 0 month (3 specimens), 6,12,18,24, 30,36 mths (2 spec) and if ordered by doctor | 0 month and at clinical diagnosis of TB | 0 month, every month till 36 months | 0 month & if any toxicity | 0 month, 6,  12, 18, 24, 30, 36 months and if ordered by doctor when patient is symptomatic | 0 month, 6, 12, 18, 24, 30 and 36 months |

### Radiographic and/or Clinical Deterioration:

a) If a patient has been admitted to the preventive therapy study and baseline sputum culture/s are reported as positive, the patient should be called up to the clinic, re-evaluated and started on chemotherapy (Category I or II depending on duration of treatment). If the patient is not suitable for Study XX, then he/she can be treated in Zero study – adequate treatment for these patients must be ensured.

b) If during the treatment period, the patient becomes symptomatic, clinical examination will be done, an X-ray ordered and 3 sputa collected for smear and culture. A course of antibiotics will be prescribed and a repeat chest X-ray done after 15 days. If the symptoms are not respiratory in origin, then evaluation and referral to the appropriate department for further investigations will be done. All attempts will be made to make a definite diagnosis including investigations like pleural tap, lymph node biopsy, ultrasound abdomen and CSF examination where necessary. The treating doctor, in consultation with TRC clinic physicians, will decide about the need for anti-tuberculosis treatment. The case will be put up to the Weekly Panel for a decision. Normally, patients diagnosed to have tuberculosis will be admitted to the Chemotherapy study (if eligible and suitable) and treated with Category II. Modifications may be made after the culture and sensitivity results are available.

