**Sample Size**

Assuming that prophylaxis will result in reduction of the incidence of TB in HIV positive persons from 7/100 person years (published TRC study) to 3/100 person years, the sample size for each arm is calculated to be 250. Allowing for a 10% drop out rate per year due to death or default, the number of patients required per treatment arm will be 325.

Total number of patients to be admitted to the study: 650

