**Randomization and Dosing**

All patients enrolled in the prevention trial will be randomized to one of the study groups using a permuted block randomization scheme of four. Stratification will be done by Mantoux reading (>5mm and ≤5mm). The group assignment list will be generated centrally before the start of trial and sequentially numbered sealed envelopes containing the study group assigned will be prepared independently. At the initiation of prophylaxis, each patient will be counseled about the importance of taking drugs regularly. Patients will be asked to return the empty packets as well as unused tablets at each monthly visit.

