**Statistical analysis and outcome measures**

The primary end point of the study will be development of tuberculosis and the secondary endpoints will include adverse drug reactions and mortality rate. The intention-to-treat approach will be used for analyzing the data for primary and secondary end points. Annual interim analyses will be done to ensure timely identification of any significant risks or benefits to patients. The treatment groups will be compared to note random distribution of baseline demographic and socio-economic, clinical and laboratory characteristics. The incidence of tuberculosis will be estimated by the person-year method. Cumulative proportion will be used for adverse reactions and mortality. The log rank test of significance will be used to compare cumulative incidence of TB in the treatment groups. Survival analyses using the log rank testing the null hypothesis and Kaplan Meier curves for depicting cumulative survival in TB and mortality will be done to compare outcomes between study groups. Multivariate analyses will be performed using Cox’s proportional Hazards model.

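### Patients whose month-0 sputum proves culture-positive after admission stay in an intention-to-treat analysis of TB incidence, with no rule separating TB already present at entry from new disease

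*Protocol*

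**What the plan says.** - **Target population.** The Protocol's Study Design section describes a "randomized clinical trial among HIV- positive patients without active tuberculosis". The section on study population and enrollment requires that TB has been ruled out by screening.
- **Baseline specimens.** In the investigation and follow-up table, the entry for sputum smear and culture begins "0 month (3 specimens".
- **Late positive results.** The section on radiographic and clinical deterioration, item a), opens with the case "If a patient has been admitted to the preventive therapy study and baseline sputum culture/s are reported as positive". It then requires recall, re-evaluation and chemotherapy, and says nothing about the analysis.
- **Analysis rule.** The section on statistical analysis and outcome measures makes occurrence of TB the primary end point, estimates incidence by person-years and compares arms by log-rank test. It adds: "The intention-to-treat approach will be used for analyzing the data for primary and secondary end points". No exception is given.

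**The concern.** The protocol foresees patients who do not belong to its own target population and who become known only after admission. Item a) says admitted rather than randomised. But all enrolled patients are randomised under Randomization and Dosing, so these patients will normally already have an arm.

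A positive culture on a month-0 specimen shows disease present before the first dose. Neither regimen could have prevented it, so it carries no information on preventive efficacy. Under unqualified intention-to-treat the patient nevertheless stays in the primary set. Two outcomes are then possible, and neither suits the question:

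- **Counted as an event:** a non-preventable case is added to that arm.
- **Kept without an event:** person-time spent on TB chemotherapy enters the denominator of an incidence rate that is meant to describe preventive therapy.

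The first has the larger consequence: dilution of the rate ratio toward 1 and loss of power. If the choice is left open, it may also be made after results by arm are known, since annual interim analyses are planned.

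**Working it through.** **Inputs from the Protocol.** Sample Size gives the rates and the number per arm: "from 7/100 person years (published TRC study) to 3/100 person years, the sample size for each arm is calculated to be 250". It gives the loss as well: "Allowing for a 10% drop out rate per year due to death or default, the number of patients required per treatment arm will be 325". Follow-up is three years from admission. Equal allocation is inferred from the equal arm sizes.

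**Assumptions.** The share f of randomised patients with a positive month-0 culture is not in the documents. I use 0.5%, 1%, 2% and 5%, equal in both arms. Rates are constant, and loss is a constant hazard of −ln(0.9) = 0.105 per year. Tests are two-sided at 5%. Cases present at entry, if counted, get an event time in the first two months (mean 1/12 year).

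**Step 1: the plan's own figure.** Three-year risks are 1 − exp(−0.21) = 0.189 and 1 − exp(−0.09) = 0.086. A two-proportion formula with 90% power and continuity correction gives 251 per arm, against the stated 250. Alpha, power and formula are not stated and other combinations also come close, so this shows only that the inputs are of the right order. The 325 is 250 × 1.30.

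**Step 2: expected events without TB at entry, 325 per arm.** With TB rate λ and loss hazard δ, person-years are 325 × [1 − exp(−3(λ+δ))]/(λ+δ), and events are λ times that.
- λ = 0.07: 758.2 person-years, 53.1 events.
- λ = 0.03: 801.3 person-years, 24.0 events.

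**Step 3: add the cases present at entry, counted as events.** Events become 325f + (1−f) × (events in Step 2). Person-years become (1−f) × (person-years in Step 2) + 325f/12.

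| f | Added per arm | Events, 7 vs 3 | Rates per 100 PY | Rate ratio | Log-rank power |
|---|---|---|---|---|---|
| 0 | 0 | 53.1 vs 24.0 | 7.00 vs 3.00 | 0.43 | about 95% |
| 0.5% | 1.6 | 54.4 vs 25.5 | 7.21 vs 3.20 | 0.44 | about 94% |
| 1% | 3.3 | 55.8 vs 27.0 | 7.43 vs 3.41 | 0.46 | about 93% |
| 2% | 6.5 | 58.5 vs 30.1 | 7.87 vs 3.83 | 0.49 | about 91% |
| 5% | 16.3 | 66.7 vs 39.1 | 9.24 vs 5.13 | 0.55 | about 83% |

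The power column comes from log-rank simulation under the same assumptions. Simulated rate ratios (about 0.42, 0.44, 0.45, 0.48 and 0.55) agree with the arithmetic to within 0.01.

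**Step 4: exclude on the month-0 specimen instead.** The rate ratio stays at about 0.42 to 0.43 and power at about 94–95% for every f in the table.

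**Step 5: cross-check by another method.** Comparing three-year risks at 250 per arm, without losses, with f + (1−f)p in place of p, the risk ratio moves from 0.454 to 0.468, 0.482, 0.507 and 0.573. Power moves from 92.1% to 91.1%, 90.1%, 88.1% and 81.6%. With exclusion, the ratio stays at 0.454 and power at 91.9%, 91.8%, 91.5% and 90.7%. The pattern is the same.

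**The case against.** The strongest reply is that intention-to-treat settles who is analysed and in which arm, not what an event is. A reader might infer from the combined sections that TB found on a baseline specimen is scored as a failure of prophylaxis. The Protocol never says so. It speaks of incidence and of TB developing, which can equally mean new disease only. This part of the objection stands, and the dilution above is conditional on counting these cases.

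A reader might also infer that the comparison is biased toward one regimen. It is not. The specimen is taken at month 0, so these cases are balanced between arms in expectation. If the regimens were equally effective, adding them would leave the test valid.

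The size is also open to challenge. Screening for TB and the exclusion of low CD4 counts may keep the share small. At 1% the loss is about two percentage points of power, and at 0.5% about one. That stands too, which is why the low shares are shown. Only the Protocol's own contrast of 7 versus 3 is used, since a smaller contrast would mix this issue with a different one.

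Finally, the SAP is not shown and may define the analysis sets. That would be a full answer if the Protocol were merely silent. But it states an unqualified rule for the primary end point and elsewhere describes patients whom that rule does not fit. An SAP exclusion would depart from the Protocol as written.

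**Conclusion.** The point holds as a cheap improvement to a stated rule. Followed literally, the analysis section keeps patients with TB at entry in the primary set, contrary to the target population, and says nothing on whether they are events. If they are counted, the cost is dilution and lost power: negligible at 0.5%, small at 1–2%, and about 12 percentage points (95% to 83%) at 5%. These figures rest on an assumed share that is equal in both arms, constant rates of 7 and 3 per 100 person-years, 325 per arm and 10% loss per year. The documents do not support a claim that such cases are already defined as prophylaxis failures, that either arm is favoured, or that type I error is inflated.

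**What to change.** In the section on statistical analysis and outcome measures, define the primary efficacy set as all randomised patients except those with a positive culture on a specimen taken at month 0. The exclusion should rest on that specimen alone, whenever the result arrives, and be applied identically in both arms. Because the specimen precedes treatment, such an exclusion does not depend on the assigned regimen. Report the number excluded per arm, and keep the analysis of all randomised patients as a sensitivity analysis that states how these patients are scored.

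The cost is a sentence or two of text, one additional analysis, a slightly smaller primary set, and an acknowledged departure from strict intention-to-treat for the primary end point. The clinical handling of these patients is not affected.
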